### Harms

No adverse events from TTM interventions have been reported in previous studies. Furthermore, in both intervention and control groups, data collection did not cause physical harm to the children and did not create psychological, social, or financial risks. If there is a risk of affecting the body (ie, pain or injury) or mind (ie, dissatisfaction, discomfort, hate, or boredom) of any participant, we decided to temporarily suspend or stop that individual’s participation and data gathering. Moreover, if any severe adverse events, such as death or other medical occurrences resulting in hospitalization, were to occur during the massage intervention sessions, the researcher planned to terminate the intervention and immediately report the event to the nearest local hospital in China. The researchers will report whether any such adverse events occurred to the ethics committee as required and describe them in the final paper.

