### Intervention

Children assigned to the TTM group received sixteen 40-to-50-minute parent-delivered TTM sessions over an 8-week period (2 sessions per week) in the health room of the school after school had finished. Gifts and rewards were given to parents and children to increase intervention adherence rates. The control group maintained a normal daily routine when in school.

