### Ancillary and Posttrial Care

Participants could contact the researchers during the trial or 1 month after participation ended. Plans were made for participants with serious adverse events to receive a timely and appropriate response.

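### The commitment to report adverse events, as worded, covers only severe events during massage sessions, so a report of none would say little about safety and could not be compared between arms

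*Protocol article*

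**What the plan says.** The Harms section of the protocol article has two tiers.

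- **Lesser harms.** "If there is a risk of affecting the body (ie, pain or injury) or mind (ie, dissatisfaction, discomfort, hate, or boredom) of any participant", that individual's participation and data gathering are suspended or stopped. Nothing is said about recording or reporting the event.
- **Severe events.** The researcher ends the intervention and notifies a hospital "if any severe adverse events, such as death or other medical occurrences resulting in hospitalization, were to occur during the massage intervention sessions".

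The reporting commitment follows the second tier directly: "The researchers will report whether any such adverse events occurred to the ethics committee as required and describe them in the final paper".

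The only sentence in that section that names the control arm is an assertion and not a rule for collecting events: "in both intervention and control groups, data collection did not cause physical harm to the children". Under Intervention, that arm has no sessions: "The control group maintained a normal daily routine when in school".

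Ancillary and Posttrial Care adds two things. One is contact started by the participant: "Participants could contact the researchers during the trial or 1 month after participation ended". The other is a care response: "Plans were made for participants with serious adverse events to receive a timely and appropriate response". Neither mentions collecting or reporting events.

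**The concern.** The word *such* carries the limits of the action rule into the reporting commitment. A session-bound trigger is reasonable for deciding when to end a session and call a hospital. As a definition of what gets reported, it applies a severity limit and a time limit together, and it leaves one randomized arm with no way to contribute an event.

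The article itself foresees lesser harms. It names pain and injury under Harms, and under TTM Procedure it mentions muscle tightness and stretches that go too deep. It also calls the trial the first RCT of parental TTM in these children and says it will support family-based care. Harms opens by noting that earlier TTM studies reported no adverse events. A zero produced by the reporting rule could be read as one more confirmation of that record.

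**Working it through.** The documents give no event rate or safety figure, so there is none to reproduce. The check is mainly of wording; the arithmetic shows how narrow the covered window is.

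**1. Which events the commitment covers**

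| Event | Action stated | Within the reporting commitment? |
|---|---|---|
| Death or hospitalization during a session (TTM arm) | End intervention, notify hospital | Yes |
| Pain, injury or distress, any participant | Suspend or stop | Not on the natural reading |
| Severe event between sessions or in follow-up | Care response | No |
| Any event in a control child | Suspension rule or care response may apply | No (no sessions) |

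**2. Covered exposure**

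Inputs: 48 children randomized 1:1, so 24 per arm (Abstract; Randomization); "sixteen 40-to-50-minute parent-delivered TTM sessions over an 8-week period" (Intervention); assessment after 8 weeks and at 2 months (Abstract). Assumptions: 2 months is about 61 days, and every child is followed throughout.

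- Sessions: 24 × 16 = 384.
- Time in sessions: 384 × 40/60 = 256 h to 384 × 50/60 = 320 h. Divided by 8,766 h per year, this is 0.029 to 0.037 person-years.
- Time on study: 56 + 61 = 117 days. For 48 children, 48 × 117/365.25 = 15.4 person-years.
- Control arm: 0 h covered.

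**3. Chance of no reportable event under the commitment**

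*Background hospitalization*, assumed at 2 to 20 per 100 child-years: P(0) = exp(−rate × person-years).
- Highest: exp(−0.02 × 0.0292) = 99.9%.
- Lowest: exp(−0.20 × 0.0365) = 99.3%.

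*Severe events caused by massage during a session*, assumed probability p per session: P(0) = (1 − p)^384.
- p = 1/100,000: 99.6%.
- p = 1/10,000: 96%.
- p = 1/1,000: 68%.

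**4. The same assumptions with wider reporting**

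- Serious events in both arms over 117 days: 1 − exp(−rate × 15.4) gives a 26%, 54%, 79% or 95% chance of at least one event at 2, 5, 10 or 20 per 100 child-years. Under the written commitment the chance is about 0.06% to 0.7%.
- Non-severe events in the TTM arm, at an assumed 5%, 10% or 20% per child: 1 − (1 − q)^24 = 71%, 92% or 99.5%.

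**5. What zero would show**

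Setting (1 − p)^n = 0.05 gives one-sided 95% upper limits of 1 − 0.05^(1/384) = 0.78% per session (sessions taken as independent) and 1 − 0.05^(1/24) = 11.7% per child. Both limits concern severe in-session events only.

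**The case against.** The strongest reply is that the quoted sentence says what to do in a session and does not say which events are recorded. The limit reaches reporting only through *such*, in a sentence that closes a paragraph also covering pain and injury in any participant. A wider reading is therefore possible. It is strained, because the suspension sentence speaks of a risk and the severe tier is the nearest mention of adverse events. Even the wider reading states no means of collecting events. Reporting to the ethics committee *as required* might bring in more, but the article does not say so.

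A reader might infer that all delayed and control-arm events are missed. The documents do not support that. The suspension rule covers any participant, the trainer monitors each session, and participants may contact the researchers. These events lie outside the reporting commitment, but they are not necessarily unknown.

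A reader might also take the window's share of time on study (10.7 to 13.3 h of about 2,808 h per TTM child, 0.4% to 0.5%) as the share of harms captured. It is a share of clock time only. Harms caused by massage need not spread evenly, and the documents do not say that they usually appear after the session.

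Two further points stand in part. Safety is not among the stated objectives, and no safety claim is announced. Details such as who asks about harms, and with what question, may properly sit in the full protocol. Neither removes the problem, which is a stated commitment with limits that do not suit reporting.

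**Conclusion.** The point holds as one about the scope of reporting. Taken as written, the commitment covers severe in-session events in the TTM arm and nothing else. A statement that none occurred would be likely under a wide range of circumstances: 99.3% to 99.9% under the assumed background rates, and 96% or more if massage caused severe in-session events in up to 1 per 10,000 sessions. It would not be assured whatever happened, since at 1 per 1,000 sessions the figure falls to 68%. No comparison of harm between arms is possible under this commitment.

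All event rates here are assumptions; none comes from the documents. The conclusion about scope does not depend on them. It rests on reading *such* as referring to the severe tier, which is the natural reading though not the only possible one.

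**What to change.** Separate the reporting commitment from the action rule for severe in-session events. Leave that action rule and the suspension rule as they are. Word the commitment to cover adverse events of any severity, in both arms, from randomization to the 2-month follow-up.

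Data collection ended on June 20, 2022, so events cannot now be sought prospectively. What remains is for the results paper to:

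- report by arm every documented event, suspension and stop, with its reason;
- state that ascertainment outside sessions and in the control arm was passive, unless the trial records show otherwise;
- not present a zero count as evidence of safety.

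The cost is one extra table, a sentence or two on ascertainment, and a less favourable safety statement.

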### Confidentiality

The research group will keep the data confidential, and the research group will use passwords to record and access data. In this study, only the research group will have access to the data, and the research group will not state the names of the participants under any circumstances if the study results are published in a journal. The participants’ personal information will be stored in a specific file with a preset code.

### Ancillary and Posttrial Care

Participants could contact the researchers during the trial or 1 month after participation ended. Plans were made for participants with serious adverse events to receive a timely and appropriate response.

### Patient and Public Involvement

The patients and public will not be involved in the design, conduct, reporting, or dissemination of this research.

## Results

We finished all data collection on June 20, 2022. Data analysis will be started, and we expect results to be published in 2023. The normal distribution of the data will be determined before descriptive statistics for all variables are calculated. The participants’ demographic information will be reported as descriptive data. The primary outcomes will be expressed as continuous variables, and generalized estimating equations will be used to evaluate the effect of TTM on the children (via the ATEC score) at 3 time points: immediate, short term, and long term. Changes in physiological parameters (ie, HRV and gait parameters) after the intervention will be analyzed. Further, the relationship between ATEC score and physiological parameters will be identified with a correlation analysis. Finally, changes in parental stress throughout the intervention period will be investigated with the PSI-4-SF.

## Discussion

This study aims to assess the effects of parent-delivered TTM in children with autism by evaluating changes in symptoms and physiological parameters (ie, gait and HRV). In practice, massage has previously been used to treat autism. However, this treatment has not been included in evidence-based practice for autism due to the lack of long-term, extensive scientific research to supports its use. At present, studies of interventions have mainly focused on qigong massage and tui na massage. Furthermore, we found that outcome measures in most prior studies were based on questionnaires and scales evaluated before and after the intervention, and that there was a lack of studies that explored the mechanisms that underlie core symptom improvement. Presumably, massage adjusts the body and mind via sensory processes [70,71] and neural and hormonal regulation (eg, changing oxytocin levels).

In comparison with prior work, this will be the first RCT to explore parental TTM in terms of its physiological and psychological effects on children with autism. We will use objective indices to investigate possible mechanisms underlying the observed effects. Our study may highlight the value of complementary and alternative therapies for adjunctive treatment of autism to enhance family-based interventions. Both parents and blinded teachers will be evaluated for effects that might cause bias. Finally, the variability of massage manipulation by parents was minimized by expert training, examinations, and supervision.

## Appendix

Multimedia Appendix 1 SPIRIT guidelines.

Multimedia Appendix 2 Parents’ consent form.

## Abbreviations

ANS: autonomic nervous system
ASD: autism spectrum disorder
ATEC: Autism Treatment Evaluation Checklist
HRV: heart rate variability
PSI-4-SF: Parenting Stress Index, Fourth Edition–Short Form
RCT: randomized controlled trial
TTM: traditional Thai massage
